## Abstract

**Background:**

Delirium is a common and serious condition, which affects many of our older hospitalised patients. It is an indicator of severe underlying illness and requires early diagnosis and prompt treatment, associated with poor survival, functional outcomes with increased risk of institutionalisation following the delirium episode in the acute care setting. We describe a new model of delirium care in the acute care setting, titled Geriatric Monitoring Unit (GMU) where the important concepts of delirium prevention and management are integrated. We hypothesize that patients with delirium admitted to the GMU would have better clinical outcomes with less need for physical and psychotropic restraints compared to usual care.

**Methods/Design:**

GMU models after the Delirium Room with adoption of core interventions from Hospital Elder Life Program and use of evening bright light therapy to consolidate circadian rhythm and improve sleep in the elderly patients. The novelty of this approach lies in the amalgamation of these interventions in a multi-faceted approach in acute delirium management. GMU development thus consists of key considerations for room design and resource planning, program specific interventions and daily core interventions. Assessments undertaken include baseline demographics, comorbidity scoring, duration and severity of delirium, cognitive, functional measures at baseline, 6 months and 12 months later. Additionally we also analysed the pre and post-GMU implementation knowledge and attitude on delirium care among staff members in the geriatric wards (nurses, doctors) and undertook satisfaction surveys for caregivers of patients treated in GMU.

**Discussion:**

This study protocol describes the conceptualization and implementation of a specialized unit for delirium management. We hypothesize that such a model of care will not only result in better clinical outcomes for the elderly patient with delirium compared to usual geriatric care, but also improved staff knowledge and satisfaction. The model may then be transposed across various locations and disciplines in the acute hospital where delirious patients could be sited.

**Trial Registration:**

Current Controlled Trials ISRCTN52323811

## Background

Delirium is a common and serious condition, which affects many of our older hospitalised patients. The prevalence in hospitalised elderly patients is shown to be as high as 50%, with the diagnosis in 11-24% of older patients upon admission and another 5-35% of them developing delirium during admission [1,2]. It is an indicator of severe underlying illness and requires early diagnosis and prompt treatment. The development of delirium is associated with increased need for nursing surveillance, greater hospital costs and in-hospital mortality rates of 25-33% and one-year mortality rate of 35-40% [3-8]. Complications may also occur related to physical injuries from agitated behaviour, complications of immobility as a result of physical restraints and pharmacologic agents used to control the behaviour in the confused patients and nosocomial infections resulting from the prolonged hospitalization [9]. This in turn translates to increases in length of hospital stay, rates of admission to nursing homes, rates of mortality, and higher healthcare costs.

The importance of delirium is highlighted by its inclusion as a marker for quality of care and patient safety by the National Quality Measures Clearinghouse of the Agency for Healthcare Research and Quality, as higher delirium rates would be expected to correlate with lower quality of hospital care after adjustment for casemix. Moreover, the Assessing Care of Vulnerable Elders Project has ranked delirium among the top 3 conditions for which the quality of care needs to be improved [10,11]. Other worldwide initiatives such as in Western Australia (WA), the Department of Health will be implementing evidenced based Models of Care (including Delirium) across WA Health with other nation-wide efforts made in UK as well.

The Asian state of Singapore has one of the fastest ageing populations in the Asia-Pacific region with 15-20% of total population consisting of persons aged 65 and above by the year 2030. A random point survey in our geriatric medicine department demonstrated a delirium prevalence rate of 15%. This potentially translates to 3,600 patients per year or 10 patients per day. The survey also showed that elderly inpatients with delirium had a longer average length of stay (ALOS)(15 days) than that of a normal geriatric inpatient (ALOS = 11 days). In addition, 50% of falls in the geriatric wards were related to delirium, resulting in an even longer ALOS of 23.9 days, thus strengthening the case for improved delirium care (data available upon request).

Studies have looked at interventions for delirium prevention in hospitalised geriatric patients [12], yet others have incorporated delirium management as part of the interventions of a consulting geriatric team [13-16] or nursing improvement protocols [17-19]. However few studies have specifically examined the impact of combined measures to improve the management of subjects with delirium (Table 1) [20-25]. The mixed results illustrated serve to highlight the heterogeneity of interventions employed and outcomes measured. Despite various differences, a common theme of these programs appears to be the application of comprehensive medical care with emphasis on intensive nursing care and education.

**Table 1 T1:** Summary of studies on delirium management in acute hospitals

Study	Subjects, n	Interventions	Outcomes	Results
Cole et al, 1994	88	• Geriatric consultation within 24 hours • Daily nursing visits • Nursing intervention protocol	• SPMSQ (memory, orientation, concentration) • CAM • CGBRS (behaviour and ADLs)	• Improvement in SPMSQ scores at 2 weeks but no difference at 8 weeks • No difference in restraint use, LOS, discharge setting, survival
Cole et al, 2002	227	• Geriatrician consult within 24 hours • Daily nurse visits • Nursing intervention protocol	• MMSE • Delirium Index • Barthel index • LOS • Survival within 8 weeks • Charlson's	• No difference in time to improvement • No difference in delirium index, Barthel, LOS, discharge setting, and survival.
Flaherty et al, 2003	196, 69 with delirium	• 24 hour intensive nursing care • Physical restraints-free policy • Comprehensive geriatric care	• Not applicable (descriptive study)	• No physical restraints used during patient hospital stay. • Lower use of pharmacological restraints • LOS equal to expected LOS
Lundstrom et al, 2005	400, 125 with delirium	• 2-day education course for staff on Geriatrics • Education for caregiver-patient interaction • Work reorganization (focus on individualized care) • Monthly staff guidance	• OBS scale • MMSE • Katz ADL • DSM IV for delirium	• Fewer patients remained delirious on day 7. • LOS lower with intervention. • Fewer deaths in subjects in intervention ward.
Pitkala et al, 2006, 2008	174	• Comprehensive geriatric assessment • Administering atypical antipsychotics instead of conventional neuroleptics • Orientation • Physiotherapy • Nutritional supplementation • Hip protectors • Cholinesterase inhibitors • Discharge planning	• Discharge destination and mortality • MMSE • Barthel • MNA • Geriatric Depression Scale • MDAS • Costs & HRQoL	• No significant difference in primary outcome (Institutionalisation and mortality) • Intensity and symptoms of delirium were alleviated faster in treatment group • Improvement in cognition at 6 months • No difference in change of function

ADL: activities of daily living; CAM: confusion assessment method; CGBRS: Crichton geriatric behavioural rating scale; DSM-IV: diagnostic and statistical manual of mental disorders, fourth edition; HRQoL: health-related quality of life; LOS: length of stay; MDAS: memorial delirium assessment scale; MMSE:mini-mental state examination; MNA: mini nutritional assessment; OBS: organic brain syndrome scale; SPMSQ: short portable mental status questionnaire.

In improving delirium care in the acute hospitalised elderly, the establishment of a specific unit for acute delirium care represents a significant step towards the systematic delivery of good geriatric care for the delirious elderly. For the current study, we describe the development of the Geriatric Monitoring Unit (GMU)- a specialised 5-bedded unit which incorporates specific room design for an elder-friendly environment, lower staff-patient ratio, coupled with structured core, program interventions and bright light therapy to reside delirious patients, supported by 24-hour intensive nursing care.

The primary aim of this study is to compare delirious patients admitted to the Geriatric Monitoring Unit (GMU), compared to usual geriatric care in general ward setting on the following primary measures: (1) Duration of delirium and severity of delirium, (2) Use of physical and chemical restraints, (3) Falls rate, (4) Physical injury rate due to agitated behavior, (5) Functional outcomes/gains in the elderly geriatric patients, (6) Morbidity (such as nosocomial infection rate, urinary catheter use and catheter days, pressure ulcer rate); (7) Patient and family satisfaction score in elderly persons with delirium. We postulate better outcomes in patients admitted to GMU versus usual geriatric care. Our secondary aims include looking at which specific aspects of the interventions would yield the greatest benefit for future translation on a larger scale; the effects of the multicomponent intervention and bright light therapy on sleep of these patients as well as their effect on antipsychotic and sedative-hypnotic use.

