12	Patients with functional decline will not benefit from early rehabilitation.

(4) Reference resources and practical reminders were made available for the staff in GMU.

(5) A continuing education program for care providers was implemented where the staff (doctors, allied health staff) involved in the GMU has regular training to increase awareness and knowledge in diagnosis and management of delirious patients.

(6) Nursing leaders helped support the trained nurses during the implementation stage.

(7) Daily geriatrician input with regards to these patients with daily documentation of mental status (Abbreviated Mental Status Test (AMT)/Chinese Mini Mental State Examination (CMMSE)) [37,38], Confusion Assessment Method (CAM) questionnaire [39] and type and severity of delirium (hyper-, hypo- or mixed delirium), Delirium Rating Scale (DRS) - severity [40], type of restraint use (physical and chemical including documentation of indication for restraint), pain assessment and medication management.

(8) Twice-weekly multidisciplinary rounds (involving the geriatricians, cognition nurse clinician, nurses, physiotherapists, occupational therapists, case coordinator, pharmacist, medical social worker, and dietician).

(9) Monthly meetings with the multidisciplinary staff members to evaluate the ongoing program, refine, voice out problems

(10) Early involvement of care co-ordinator or medical social worker (where appropriate) in discharge planning.

GMU core interventions are performed daily (see Table 3) and incorporated via a structured protocol into the daily nursing workflow and documentation sheet.

**Table 3 T3:** GMU Core interventions

1.	No mechanical restraints and where possible, no pharmacological restraints. After trying all non-pharmacological methods and patient proves to be a danger to himself and others, then antipsychotics and sedative-hypnotics are used carefully at the lowest possible dose and to tail down the dose and remove the pharmacological agent once not required.
2.	Thrice daily patient orientation via reality orientation board
3.	Early mobilization with the help of therapists and trained nurses
4.	Provision of visual aids (such as eye glasses) if available
5.	Providing adequate hearing aids/earwax disimpaction where necessary with the use of portable audio amplifier
6.	Oral volume repletion/feeding assistance with scheduled oral intake schedule

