**Morbidity and mortality**	**Rate of falls** **Physical injuries** **Urinary catheter usage** **Pressure ulcer development** **Rate of nosocomial infections** **Inpatient mortality**	X	X	X
**Qualitative measures**	**Family satisfaction survey** **Staff satisfaction survey** **Staff knowledge survey**	-	X	X
**Follow-up data (6, 12-monthly)**	**Rate of hospitalization** **Functional status (BI)** **Institutionalisation** **Mortality**	-	X	X

The primary outcome measures we will look at include: (i) Clinical data with regards to duration and severity of delirium; frequency of use of physical restraints, use of pharmacological agents/sedative hypnotics, physical injuries or monthly falls rates; and nosocomial infection rates (ii) Functional outcomes by way of modified Barthel Index score and (iii) Patient/family satisfaction score; all adjusted for baseline demographics and comorbidities. We aim to look at the outcomes measures of patients with delirium admitted to GMU versus those managed under usual care (control group)(refer to Figure 1).

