##### Sample size and statistical analyses

We aim to recruit 50 subjects during the pre-implementation and 50 subjects each from the GMU group and control (usual care) group (total 150 study subjects). We based our calculations on a two-sample comparison of means for the GMU and control group using non-repeated measures. Using mean Barthel Index score difference of 10 with standard deviation of 14 with ratio between groups of 1, a sample size of 45 patients in each group will be adequately powered to detect a 10-point mean Barthel Index group differences, with 90% power. Assuming that 10% of patients are lost to follow-up at 1 year, we project a final sample size of 50 (rounded up). Level of significance was set at 5%. Sample size calculation was performed in PS Power and Sample Size Calculations V2.1.30. Statistical analysis will be performed using appropriate statistical methods (univariate and multivariate analyses) for between group comparisons. Appropriate statistical methods will be used for the longitudinal outcome analyses and statistical significance is set at 5%.

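### The aims and the methods give different primary outcome lists of up to 12 measures, with one 5% level, no lead outcome, and power stated for the Barthel Index only

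*Protocol article*

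**What the plan says.** The protocol article names its primary outcomes twice.

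- **Background, aims paragraph.** GMU and usual care are compared "on the following primary measures: (1) Duration of delirium and severity of delirium, (2) Use of physical and chemical restraints, (3) Falls rate". Headings four and five add injuries linked to agitation and functional gains, and heading seven adds satisfaction of patients and relatives. Heading six is left open: "6) Morbidity (such as nosocomial infection rate, urinary catheter use and catheter days, pressure ulcer rate". The same paragraph places the effect on antipsychotics and sedative-hypnotics among the secondary aims, although chemical restraint stands under the second primary heading.
- **Data collection, paragraph after Table 4.** The second list opens with "The primary outcome measures we will look at include: (i) Clinical data with regards to duration and severity of delirium". Its clinical group then goes on to name "frequency of use of physical restraints, use of pharmacological agents/sedative hypnotics, physical injuries or monthly falls rates; and nosocomial infection rates". The modified Barthel Index and a satisfaction score complete it.

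Sample size and statistical analyses builds the calculation on the Barthel Index only: difference 10, SD 14, 45 per group, 90% power, raised to 50 for 10% loss at 1 year. It adds "Level of significance was set at 5" per cent and repeats that level for the analyses. It does not say which primary measure leads.

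Table 3, item 1, reads "No mechanical restraints and where possible, no pharmacological restraints". Item 10 tells staff to keep immobilising equipment, urinary catheters included, to a minimum.

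**The concern.** Which outcomes are primary is a decision for the protocol, and here the protocol gives two answers. A pressure ulcer or catheter result would be primary under the aims but not under the methods. Sedative-hypnotic use is primary under the methods and a secondary aim in the Background.

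The outcome that fixed the sample size is only one item in either list and has no special standing. With many measures of equal rank and one 5% level, a reader of the results cannot tell which comparison decides the trial. The more measures that count as primary, the likelier it is that one of them is significant by chance.

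**Working it through.** **1. The plan's own sample size.** Inputs, all from Sample size and statistical analyses: difference 10, SD 14, ratio 1, 90% power, 5% level. Sidedness is not stated.

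- Two-sided normal formula: n = 2 × [14 × (1.960 + 1.282) / 10]² = 41.2, so 42 per group.
- Two-sided t-test: 42.2, so 43 per group, within two of the stated 45.
- One-sided normal formula: 34 per group, which does not fit 45.
- Power with 45 per group: 92.3% (normal), 91.8% (t-test).
- Loss to follow-up: 45 / 0.90 = 50, as stated.

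The sample size is sound for the Barthel Index and fits two-sided testing, which is assumed below.

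**2. Counting the two lists.**

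| Measure | Background aims | Data collection |
|---|---|---|
| Delirium duration | primary | primary |
| Delirium severity | primary | primary |
| Physical restraint | primary | primary |
| Chemical restraint / drug use | primary as chemical restraint; antipsychotics and sedative-hypnotics also a secondary aim | primary, naming sedative-hypnotics |
| Falls | primary | primary, joined to injuries by an 'or' |
| Physical injury | primary | primary, as above |
| Function | primary | primary (modified Barthel Index) |
| Nosocomial infection | primary | primary |
| Urinary catheter use | primary | absent |
| Catheter days | primary | absent |
| Pressure ulcer | primary | absent |
| Satisfaction | primary | primary |
| **Count** | **12 (7 headings)** | **8 or 9** |

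The first count is 13 if patient and family satisfaction are separate scores. The second is 8 if falls and injuries are one measure and 9 if they are two.

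**3. False-positive rate if each measure is tested once, two-sided at 5%, with no true differences.** Under independence, the chance of at least one significant difference in either direction is 1 − 0.95^k. Each two-sided test puts 2.5% in GMU's favour, so the chance of at least one false result favouring GMU is 1 − 0.975^k.

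| k | Either direction | Favouring GMU |
|---|---|---|
| 7 | 1 − 0.95^7 = 30.2% | 1 − 0.975^7 = 16.2% |
| 8 | 33.7% | 18.3% |
| 9 | 37.0% | 20.4% |
| 12 | 1 − 0.95^12 = 46.0% | 1 − 0.975^12 = 26.2% |

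**4. Allowing for correlation.** The article gives no correlations, so equal pairwise values of 0.3 and 0.5 are assumed (normal test statistics, 400,000 simulated draws, critical value 1.96).

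| k | Correlation | Either direction | Favouring GMU |
|---|---|---|---|
| 7 | 0.3 | 27.1% | 13.7% |
| 7 | 0.5 | 23.0% | 11.5% |
| 12 | 0.3 | 39.9% | 20.3% |
| 12 | 0.5 | 31.9% | 15.9% |

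**The case against.** The strongest reply is that this is a condensed article. A separate analysis plan may hold a hierarchy or a multiplicity rule, and the analysis sentences defer to appropriate methods. That stands as far as it goes: a missing adjustment is not, by itself, the finding. It does not reach the two conflicting lists, which are in the text shown.

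It can also be said that both lists are open (one offers examples, the other says what the outcomes include), and that catheter use and pressure ulcers are still collected under Table 4. This narrows the conflict to labelling. But the label is what says which results carry the trial's conclusion.

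Four stronger readings are tempting, and the article does not support them.

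- A reader might take 30–46% as the chance of falsely finding GMU better. It is the chance of a false difference in either direction. The directional range is 16–26%. One-sided 5% tests would make 30–46% directional, but the stated 45 per group does not fit a one-sided calculation.
- A reader might infer that one significant measure suffices for success. The article postulates better outcomes and states no success rule of any kind.
- A reader might dismiss restraint and catheter results as mere compliance. Table 3 does target them directly. Yet the Abstract makes less need for restraint part of the hypothesis, and the Background links physical restraint to complications of immobility. A difference there partly reflects adherence to unit policy, which is a caution in interpretation and no ground for discarding the measure. Nor is a policy-driven difference a false positive: leaving out physical restraint, catheter use and catheter days gives k = 9, or 37% and 20%.
- A reader might assume that the trial is sized on the 12-month Barthel Index. One year appears only in the loss allowance.

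**Conclusion.** The point holds. The protocol article contradicts itself on which outcomes are primary, names up to 12 of them, and powers one without giving it priority. Independence gives the upper end of the false-positive range, since pairs such as catheter use and catheter days, or falls and injuries, are likely to be positively correlated. For all 12 measures at the assumed correlations, the risk is about 32–40% in either direction and 16–20% in favour of GMU, against 5% and 2.5% for a single two-sided test.

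These figures assume one two-sided 5% test per measure and no adjustment. That is a natural reading of the single stated level, but it is not said outcome by outcome. The lower end of each independence range counts seven headings as seven tests, the upper end 12 separate measures. The sample size calculation is not in question.

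**What to change.** - Put one identical primary outcome statement in the Background and Data collection sections.
- Make the modified Barthel Index, GMU versus concurrent control, the single primary outcome, since it is the only powered measure.
- Have the sponsor name one time point for it; the 1-year loss allowance suggests 12 months but does not state it.
- Say how deaths before that time point are handled. The Background cites one-year mortality of 35–40% in delirium, well above the 10% loss allowance. The exclusions for dangerously ill and terminal patients may lower it here.
- Make the remaining measures secondary, reported with confidence intervals or tested with Holm adjustment, and give antipsychotic and sedative-hypnotic use one status throughout.
- When reporting restraint and catheter results, note that Table 3 items 1 and 10 target them directly.

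**Cost.** The relabelling needs no new data or patients. Choosing the time point and the handling of deaths takes a real decision and may mean revisiting the loss allowance. The trial gives up the option of claiming primary success on whichever measure turns out significant. Keeping many co-primaries would cost more: Bonferroni over 12 (0.05 / 12 = 0.0042) cuts Barthel power at 45 per group from about 92% to about 70%, and over 7 to about 76%. Restoring 90% would take 68 or 62 per group before losses.

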## Methods/Design

### Project overview

The GMU concept was developed via an evidence-based approach using specific interventions that have been found to be beneficial for delirium care. GMU incorporated specific measures from the following programs: (i) Delirium Room which provides comprehensive medical care with multidisciplinary team meetings, initial behavioural and appropriate non-pharmacological methods being first line management in these patients [22] (ii) Concept of structured core interventions in Hospital Elder Life Program (HELP) [26-30] (iii) Use of bright light therapy to establish healthy sleep-wake cycle with appropriate timing to effectively shift altered circadian sleep-wake cycle to desired phase. In elderly patients with advanced sleep phase syndrome (ASPS), it has been found that evening exposure to bright light on daily basis can be beneficial [31-37]. This can be done with either a bright light box 1000-3000lux or spending time in outdoor sunlight 1-2 hours daily during late afternoon and evening.

The development of the GMU program included key considerations for room design and resource planning, program specific interventions and daily core interventions.

